### Identifying the Follow-up Patients

The study participants will have a colored sticker attached to their OPD card during their first visit. The assistant will provide a unique code to the study participants, which will be written on top of the colored sticker attached on their OPD card. Thus, during the follow-up visit, the participants will be easily identified by this colored sticker with the unique code in their OPD card. The assistant will match the unique code of the patient with the computer records and find out the study group of the patients in each follow-up visit.

In case the patient card is lost or if the patients comes with a new OPD card during follow-up, the earlier registered medical record number will not match with the new medical record number. In this case, the patient’s identity will be confirmed by matching the patient’s name, gender, age, guardian’s name, and guardian’s phone number.

### Compliance to Follow-up

The participants’ first visit to the hospital and the scheduled 3 follow-up visits need to be completed for them to be considered compliant to the follow-up. Only those participants who complete the first follow-up will be considered for second follow-up, and only those coming for second follow-up will be considered for third follow-up [6]. The patient will be considered compliant to follow-up if he or she comes within the window period of 2 days. The rescheduling of the next follow-up date will be calculated from the attended date as per the follow-up schedule for each ocular condition.

The purpose of observing compliance to follow-up is to determine the impact of counseling and reminders through SMS texts and phones call for the increment of the proportion of children completing their 3 follow-up visits based on the developed proforma and to find out the significant proportion in the follow-up rate between the 3 different groups.

### Record Maintenance

Records of the participants from the first visit to all the follow-up visits will be maintained in the department by the assistant. The details will be entered for each participant as per the proforma. If both parents accompany the child, only the mother’s detail will be included. However, when both parents accompany the child but only the father has access to a mobile phone, his details will be recorded.

The record of the patients will be kept even if they come for follow-up beyond the set window period (2 days); however, in this case, they will not be considered compliant to follow-up.

The assistant will also assign the patients to a group (regardless of whether they receive an intervention) as per the study procedure. A follow-up recording file (3 in number, 1 each for routine standard care, counseling, and reminders through SMS texts and phone calls) will be maintained. These follow-up details will also be entered in the Excel sheet on the same day as a backup in case the paper records are lost or destroyed. The entry of all the details from the proforma will be entered and stored in an Excel sheet by the assistant. The status of record maintenance will be regularly monitored by the ophthalmic officer (BP). The assistant will also be responsible for tracking the follow-up visits and updating the schedule for executing the reminder SMS texts and phone calls (Multimedia Appendix 5).

### Data Collection and Management

In order to obtain the required data from the participants, a proforma has been designed based on variables pertaining to sociodemographics and follow-up. The proforma has been developed in the English language, and the sequence of questions will be carefully looked into. Questions are arranged in the following manner: the first pertain to identification, are followed by those pertaining to sociodemographic information, and are concluded by questions pertaining to follow-up points.

#### Training of the Team

All team members will receive training on the study process. The principal investigator (MS) or coprincipal investigator (GB) will brief the team on the process during the training session, including on the consent of the participant, being polite and considerate, the standardized delivery of questions, and the noting of the responses. During the training sessions, each and every question will be explained to the team, and queries will be addressed.

#### Data Editing

Data will be submitted as early as possible to the investigator team so that they can edit the proformas and make them ready for data entry.

#### Data Entry and Validation

The data entry program will be designed in Excel. The study optometrist and coprincipal investigator will do the data entries. Corrections will be made where required by the study’s ophthalmic officer, who will compare the computer data file with the original proforma.

#### Data Monitoring and Confidentiality

The data monitoring will be performed by an internal monitoring committee on a weekly basis. All the information collected will be stored only with the investigators. The publications will not reveal any private information of any of the participants.

#### Data Analysis

Data will be processed and analyzed using Excel (Microsoft) or Epi Info (Centers for Disease Control and Prevention).

#### Univariate Analysis

Univariate logistic regression analysis will be conducted by comparing 2 variables for each variable of interest using odds ratios (ORs) and their 95% CIs. The likelihood ratio test will be used to estimate ORs and 95% CIs for all associations of interest.

#### Multivariate Analysis

Multivariate logistic regression analysis will be performed to adjust for the simultaneous effects of multiple factors on the outcome variable. The criteria for inclusion of factors in the multivariate analysis are to include all variables from the univariate analysis with a *P* value of .1 along with all the variables of known importance. To assess the importance of each variable included in the model, the Wald statistic for each variable will be used.

Before the multivariate analysis is conducted, the association among independent variables will be checked by a chi-square test. For independent variables having more than 2 categories, dummy variables will be created. All the variables meeting the above selection criteria will be entered one by one, starting with the highly significant factors from the univariate analysis. The overall significance of independent variables in the model will be assessed by likelihood ratio test (G statistic). Selection of the final model will be based on parsimony, biological interpretability, and statistical significance. The parameters of the logistic regression model will be estimated by the maximum likelihood method. The adjusted ORs and their 95% CIs will be computed using the estimates of parameters of the final model. The dependent variable will be dichotomous: either compliance with the follow-up instruction has increased, or it has remained changed (no difference) from before the intervention study to after it. The final model will be tested for goodness of fit by Hosmer- Lemeshow chi-square (*Χ*^2^) statistic. *P* values will be noted to assess the model fit. Imputation and intention to treat analysis will also be conducted (if required).

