## Introduction

Childhood visual impairment and blindness remains an important public health issue. It is estimated that around 14 million children in the world are blind [1]. The Nepal Pediatric Ocular Disease study found that the prevalence of blindness and visual impairment in the community was 0.068% (95% CI 0.02-0.12) and 0.097% (95% CI 0.04-0.15), respectively [2]. Increasing the global knowledge base for planning for childhood eye care services is a top priority in order for children with visual impairment to realize their full visual potential [3]. Follow-up of pediatric patients is important for their regular ocular morbidity monitoring, especially for amblyopia management [4]. Bharatpur Eye Hospital (BEH) observed that there was poor adherence to follow-up visits. An exploratory observation of data of the first week (January 1, 2010, to January 7, 2019) revealed that the follow-up compliance was very low among children aged 0 to 16 years in the pediatric department. Among the children advised for follow-up, only 22% were found to have come for at least 1 follow-up visit. A problem analysis showed that a lack of awareness in children and their parents regarding the importance of follow-up and patients forgetting dates of the follow-up visit (usually when there is long gap for follow-up) may be the major contributing factors for poor adherence to follow-up.

A study from India revealed that distance and cost were major barriers, as was the inability of the eye care center to communicate the importance of follow-up [5]. Another study done in Nepal found poor follow-up rates for patients following cataract surgery, which, however, improved after implementation of a high-quality pediatric counseling service, follow-up program, tracking system, and cell phone reminders [6]. Many studies have compared different methods of reminder options like telephone calls, email, and SMS text messaging in order to improve the compliance to follow-up [7-10]. Hence, a public health intervention study has been planned to estimate the effect of intervention package (counseling and reminder SMS texts and phone calls) for improving the follow-up rates in pediatric patients.

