## Methods

### Study Design and Setting

This public health intervention study will be conducted at Hiralal Santudevi Pradhan Institute of Ophthalmic Sciences which includes 13 satellite clinics and 1 base hospital (Bharatpur Eye Hospital [BEH]). The study participants will be enrolled only from the pediatric department of BEH, a centrally located tertiary eye hospital in the Chitwan district of Nepal. All pediatric patients 0 to 16 years of age meeting the inclusion criteria will form the study population. In the pediatric department of BEH, children aged 0 to 16 years are being examined as per the hospital policy.

The inclusion criteria are all pediatric patients 0 to 16 years of age advised for at least 3 follow-up visits within a 6-month period at BEH, parents or guardians of children who own a mobile phone or have daily access to a phone and are able to use the SMS text feature on these phones, and parents willing to enroll their children in the study.

The exclusion criteria are children who require fewer than 3 follow-up visits, children with ocular conditions requiring daily follow-up visits (because it is not feasible to send the reminder phone call and SMS text for daily follow-up), children who have already been treated and are under regular follow-up, children with ocular conditions requiring follow-up beyond 6 months, parents or guardians of the children who are not willing to participate in the study, and those who have been called but do not answer after 3 attempts

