### Outcomes

The primary outcome is the proportion of children completing all 3 follow-up visits in the routine standard care group, counseling group, and reminders through SMS texts and phone call group.

The secondary outcomes include the effect of parental or guardian education status in compliance to follow-up, the visual status of the children in subsequent follow-up visits, the effect of traveling distance and cost in compliance to follow-up, and the cost-effectiveness of the intervention.

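### The logistic model's dependent variable is a before-to-after change in compliance, for which the protocol describes no pre-study measure and which contradicts its own primary outcome

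*Protocol article*

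**What the plan says.** The analysis text names a dependent variable once, under Multivariate Analysis. It is to be dichotomous: "either compliance with the follow-up instruction has increased, or it has remained changed (no difference) from before the intervention study to after it".

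Other sections define the outcome differently:

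- Outcomes: "The primary outcome is the proportion of children completing all 3 follow-up visits in the routine standard care group, counseling group" and the reminder group.
- Compliance to Follow-up, at the level of the child: the first visit and the "scheduled 3 follow-up visits need to be completed for them to be considered compliant to the follow-up", with a window of 2 days. Record Maintenance adds that late attenders are recorded but not counted as compliant.
- Compliance to Follow-up also gives the purpose, which includes "to find out the significant proportion in the follow-up rate between the 3 different groups".

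On what is known of a child before the study:

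- Record Maintenance: "Records of the participants from the first visit to all the follow-up visits will be maintained in the department by the assistant".
- The exclusion criteria remove "children who have already been treated and are under regular follow-up".
- The Introduction reports, for children seen in the department in an exploratory week of data, that "only 22% were found to have come for at least 1 follow-up visit".

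**The concern.** A logistic regression models one binary value per child. 'Increased since before the study' is a change, so it needs two values per child, one from before and one from after. The article describes collecting only the second. The definition also gives no place to a child whose compliance fell.

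It is also a different quantity from the primary outcome. Completion of all 3 visits, compared between groups observed at the same time, is a between-group contrast. A before-to-after change is not, and nothing in the sentence ties it to study group. If the sentence were followed, the regression would not estimate what Outcomes says the trial is about. If it were set aside, the analyst would have to choose the outcome variable at the time of analysis, which a protocol is meant to prevent.

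**Working it through.** The point is about a definition, so the main check sets the sections side by side.

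**1. What the stated variable needs.** For child *i*, 'increased' means C(after, *i*) > C(before, *i*), so both terms are required.

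**2. What the article supplies.**

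- C(after, *i*): supplied. Compliance to Follow-up gives a yes/no rule (3 scheduled visits, 2-day window).
- C(before, *i*): not supplied. Records start at the first visit. Data Collection and Management describes a proforma with identification, sociodemographic and follow-up items. The proforma itself is an appendix that is not shown, but no section of the article mentions pre-study compliance.

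**3. Whether the 22% can stand in for C(before, *i*).** It cannot, for three reasons.

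- It is one rate for a department, so it is the same number for every child and not a child-level value.
- It comes from other children.
- It counts at least one visit, whereas the outcome counts all 3. The second dry run, under Results, shows that these are different scales: 7 of 38 children (7/38 = 18.4%) attended a follow-up visit, and all 7 had attended only the first. The article does not say how many later visits were already due, so this shows the distinction and does not estimate all-3 completion.

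**4. Whether the categories are complete.** A change can be up, none or down. The sentence names the first two. Its wording for the second is garbled, and 'unchanged' was presumably meant. Making that correction leaves the before/after definition, and the missing third category, as they are.

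**5. Whether the sample size fits a change score.** The inputs under Sample Size are proportions 0.50 and 0.25, significance level .05 with 3 comparisons, 80% power and 10% loss. Sidedness is not stated, so I took a two-sided test with pooled variance and no continuity correction:

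- α = 0.05/3 = 0.0167, z = 2.394; for 80% power, z = 0.842; mean proportion 0.375
- n = [2.394 × √(2 × 0.375 × 0.625) + 0.842 × √(0.5 × 0.5 + 0.25 × 0.75)]² / 0.25² = 77.1, rounded up to 78 per group
- 78 / 0.9 = 86.7, rounded up to 87 per group; 87 × 3 = 261

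This is close to the stated 264 (3/264 = 1.1% below). With α taken literally as the printed .02, the same method gives 74, then 83 per group and 249 in total. In either case the calculation compares two groups on a binary attendance outcome. It contains no baseline value and no within-child change. The trial was therefore sized for the outcome in Outcomes, not for the variable in Multivariate Analysis.

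**The case against.** The strongest reply is that the right variable is already in the document. Outcomes, Compliance to Follow-up and Record Maintenance agree with one another, and one garbled sentence disagrees with all of them. A sensible analyst would use the compliance definition. This stands as far as it goes: the trial does not lack a usable binary outcome. It does not rescue the sentence, which is the only one that tells the analyst what to model.

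A second reply is that the model may not be the primary comparison. Independent Variables lists only sociodemographic factors and not study group, so the regression may serve the secondary question of which factors go with compliance, and the primary test may sit in a plan that is not shown. This is fair, and I do not claim that the primary test is missing. But a model of factors associated with compliance also needs compliance as its outcome, so the stated variable is wrong under either reading.

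Several stronger readings are tempting, and the documents do not support them:

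- *The exclusion criteria prove that no enrolled child has an earlier compliance history.* They remove children already treated and under regular follow-up. A child with an earlier, lapsed visit is not clearly ruled out. What can be said is that the article describes no collection of such a value.
- *The investigators will compare with the historical 22%, and COVID-19 will then bias the result.* The hypotheses are worded as rises from 22%, which may explain the sentence, but no section proposes that comparison as the analysis. Ethical Approval reports slow enrolment (154 of 264) during the pandemic and says nothing about changed attendance.
- *The mismatch with the 22% can be given a size.* If a share r of attenders returned for each later visit, all-3 completion would be 0.22 × r², which is 5.5% at r = 0.5 and 14.1% at r = 0.8. These values of r are assumptions without a source in the article. The result would describe a hypothetical workaround, not the defect.

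**Conclusion.** The point holds as an internal contradiction in a stated analysis rule. The dependent variable under Multivariate Analysis requires a pre-study compliance value that the article nowhere describes collecting. It omits a decrease, and it conflicts with the outcome and the comparison set out under Outcomes and Compliance to Follow-up. This is a wrong statement, not an omission that an analysis plan would be expected to fill.

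Taken literally, the rule gives no derivable value for any of the 264 planned children. Taken together with the rest of the article, the intended variable can be recovered, so the harm is an outcome left open to choice at analysis and not an analysis that is impossible. No numerical bias can be attached to it from the documents. The conclusion assumes that the proforma, which is not shown, does not record pre-study compliance. If it did, the conflict with the primary outcome would remain.

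**What to change.** Replace the sentence under Multivariate Analysis with:

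*The dependent variable is compliance (yes/no) as defined under Compliance to Follow-up: all 3 scheduled follow-up visits attended within the 2-day window.*

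Delete the before/after wording. Add study group to Independent Variables and keep it in the model, so that intervention effects are estimated as contrasts between the concurrent groups. With two indicator variables for three groups, all 3 pairwise contrasts foreseen under Sample Size can be obtained.

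The cost is one sentence and one added variable. The data are already being collected, the sample size calculation is unchanged, and the change should be dated before the groups are compared.

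Which children enter the analysis, in particular the exclusion of participants who do not answer reminder calls, is a separate matter. This edit does not settle it and should not be worded as if it did.

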### Sample Size

Bonferroni correction (level of significance *P*=.05; k=3 comparisons) was adopted for sample size calculation with consideration to the proportion of attendance in counseling (p1) and reminder SMS texts and phone calls (p2) as 50% (0.5) and 25% (0.25), respectively. An estimated sample size of 264 pediatric patients will be targeted with an adjusted significance level of .02, 80% power, and 10% loss to follow-up.

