## Discussion

This study will reliably document not only the factors associated with follow-up rate through an intervention package (counseling and reminders through SMS texts and phone calls) but also the cost effectiveness of the intervention package. Compliance to follow-up visits is important for better outcomes of treatment for any condition. It is equally important for children with visual problems to comply with the follow-up so that they can receive complete treatment and be prevented from going permanently blind in some cases. Different studies have shown varied results regarding the effect of these interventions. Follow-up rates have found to be improved with these types of intervention in some studies while other studies show no significant improvement with the interventions [12-17]. One intervention may work better than others in some studies. We are testing these interventions to improve the follow-up rate of pediatric patients with ocular problems. Loss or noncompliance with the scheduled follow-up visits by patients who have been advised to come for follow-up is a major issue in many areas of clinical practice. Noncompliance has been a major problem with pediatric patients undergoing treatment at the Pediatric Ophthalmology Department at BEH, where only 22% of those advised attended the follow-up. Therefore, this study is attempting to determine which intervention strategy would work better for this problem. Any intervention found effective will be applied to other departments and will be implemented as the hospital policy in the future.

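### Attendance is the endpoint, yet intention to treat is optional and unanswered calls remove children from the reminder group only, so the primary denominator is not fixed

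*Protocol article*

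**What the plan says.** **Endpoint.** Under Outcomes, "The primary outcome is the proportion of children completing all 3 follow-up visits" in each of the three groups. Under Compliance to Follow-up, the first visit and the "scheduled 3 follow-up visits need to be completed for them to be considered compliant to the follow-up", and "The patient will be considered compliant to follow-up if he or she comes within the window period of 2 days". The same section makes the visits sequential: "Only those participants who complete the first follow-up will be considered for second follow-up". Under Record Maintenance, a child who comes outside the window stays on record; "however, in this case, they will not be considered compliant to follow-up".

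**Sample size.** "An estimated sample size of 264 pediatric patients will be targeted with an adjusted significance level of .02, 80% power, and 10% loss to follow-up". The article does not say who counts as lost when the outcome is attendance.

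**Analysis set and missing data.** The only statement closes the Multivariate Analysis section: "Imputation and intention to treat analysis will also be conducted (if required". It gives no trigger for either analysis and does not say what would be imputed.

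**Exclusion after allocation.** The section on the SMS text and phone call reminder group takes a participant out of the study when 3 call attempts go unanswered. The exclusion criteria under Study Design and Setting repeat the rule. The counseling and routine care groups receive no reminder calls.

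**The concern.** When the outcome is coming back, not coming back settles it. Every allocated child can be classified from the attendance record, and including all of them should be the primary analysis. The plan instead makes that analysis an optional extra, offers imputation of an unnamed quantity, and carries a loss allowance suited to an outcome that goes unmeasured when a patient stays away.

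This goes beyond detail that a condensed article may leave out, because one exclusion rule is written down and can act in one group only. A family that cannot be reached by phone is plausibly also less likely to attend. Removing such children takes mainly failures out of the reminder group, while comparable children stay in the denominators of the other two groups. The reminder-versus-control contrast, one of the two primary objectives, would then be biased in favour of reminders.

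**Working it through.** **1. Reproduce 264.** Inputs from Sample Size: rates 0.50 and 0.25, 3 comparisons, 80% power, 10% loss. Assumed: two-sided test. The printed .02 is .05/3 = .0167 rounded.

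- Average rate = (0.50 + 0.25)/2 = 0.375
- n = 2 × 0.375 × 0.625 × (2.394 + 0.842)² / 0.25² = 78.5, so 79 per group
- 79/0.9 = 87.8, so 88 per group; 3 × 88 = **264**

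The pooled-variance formula gives 78 per group, then 87, and 261 in total. Without the allowance the totals are 3 × 78 = 234 or 3 × 79 = 237. The 10% is therefore built into the target, and the calculation treats 264 × 0.10 ≈ 26 children as not evaluable.

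**2. What the allowance does to power.** Pooled-variance normal approximation, 50% vs 25%, alpha .05/3:

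| Analysed per group | Power |
|---|---|
| 79 | 81.1% |
| 88 | 85.7% |

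If everyone is scored, power rises. The allowance causes no bias; it only makes N larger than the formula needs.

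**3. Exclusion in the reminder group only.** Let p be the true compliance rate, d the share of the group removed, and a the compliance rate among those removed. The observed rate is (p − d·a)/(1 − d). If a = p there is no bias. If a = 0 (all removed children are non-attenders) it becomes p/(1 − d), the largest possible inflation. The documents give no figure for d or a. The range below is assumed, with a = 0, and control stays at 22%:

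| d (assumed) | True 22% reads | True 25% reads |
|---|---|---|
| 5% | 23.2% | 26.3% |
| 10% | 24.4% | 27.8% |
| 20% | 27.5% | 31.3% |
| 30% | 31.4% | 35.7% |

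At d = 10%, about 9 of 88 children, a null effect appears as 24.4 − 22.0 = 2.4 points. The hypothesised 3-point effect (22% to 25%, end of the Introduction) appears as 27.8 − 22.0 = 5.8 points.

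**4. Equal removal from all groups, for comparison.** If 10% of every group, all non-attenders, were dropped or imputed at the rate of the rest, 22%, 25% and 50% become 24.4%, 27.8% and 55.6%. Each rate rises, but the reminder contrast moves only from 3.0 to 27.8 − 24.4 ≈ 3.3 points. Material bias in that contrast needs unequal removal, which is what the call rule can produce.

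**5. Can the 10% be the non-attenders?** The planning rates imply 50% and 75% non-compliance. The Introduction's 22% implies 78% who did not return. In the second dry run 31 of 38 (81.6%) attended no follow-up visit, although that run lasted 1 month and some visits may not yet have been due. Ten percent is far below all of these, so it must mean a smaller group that the article does not name.

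**The case against.** A reader might infer that the plan drops or imputes non-attenders and so inflates compliance in every group. The documents do not support that. Read strictly, the compliance rule and the late-attendance rule already score these children as failures. Record Maintenance also has group assignment recorded whether or not the intervention is received. Imputation has legitimate objects here: covariates, and visual status at later visits, which is truly unobserved in children who stay away.

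A reader might also infer that the 10% lost are the same children as the non-attenders. The Discussion comes close to this ("Loss or noncompliance with the scheduled follow-up visits by patients who have been advised to come for follow-up is a major issue"), but that is a general remark and not a definition, and step 5 shows that the figures do not fit. The allowance is conservative and harms nothing by itself.

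Finally, missing-data rules are often left to an analysis plan, and none is shown. That would answer a complaint about absent detail. It does not answer two things the article does state: intention to treat is conditional, and unanswered calls lead to exclusion. Taken together, these leave the primary contrast exposed.

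**Conclusion.** The point holds as a failure to fix the primary denominator. It is certain from the text that attendance is the endpoint, that intention to treat and imputation are conditional with no stated object or trigger, that loss to follow-up is undefined, and that the call rule can remove children from the reminder group alone. General inflation of compliance by dropping or imputing non-attenders is a risk left open, not a rule of the plan.

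The size is illustrative. With 10% of the reminder group removed and all of them non-attenders, the reminder rate is overstated by 2.4 points (true 22%) or 2.8 points (true 25%), about as much as the 3-point effect hypothesised. Both conditions are assumptions, and the bias shrinks to zero as attendance among the excluded approaches that of the rest. The 22% describes at least 1 visit, so it only stands in for 3-visit compliance in control.

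**What to change.** 1. **Multivariate Analysis.** Replace the conditional sentence with wording to this effect: *The primary analysis includes every allocated child in the allocated group, including reminder participants who do not answer calls. Any child who does not complete all 3 follow-up visits within the window is scored as non-compliant. The compliance outcome is not imputed; imputation is limited to covariates and to other outcomes such as visual status.*
2. **Exclusion criteria and reminder-group section.** Reconcile both with this, so that an unanswered call is recorded but the child's attendance is still tracked and analysed.
3. **Sample Size.** Define loss to follow-up (for example, withdrawal of consent) or delete it. State that with all 88 per group analysed the power for 50% vs 25% at .05/3 is about 86%, against 81% with 79 per group.

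The cost is a change of wording in three places. No extra patients are needed, and the assistant already tracks follow-up visits. Children already excluded for unanswered calls should be put back where hospital records show their attendance. Reported compliance may be slightly lower, and the reminder estimate will include families who could not be reached. That is the relevant quantity if the hospital means to adopt reminders as policy.
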